### Dietary intake

Dietary intake will be measured by the AES Heart, a food frequency questionnaire that is an extended version of the adult Australian Eating Survey. The AES Heart captures additional details regarding fat and salt intakes, and foods or nutrients evidenced to reduce cholesterol. The AES Heart is an online tool that provides immediate personalised feedback on eating habits related to heart health. The AES Heart was previously validated for long-chain fatty acids and used to estimate dietary intake over the 3–6 months, reflecting time since last follow-up [28]. The version used in this study has been slightly modified to be administered online and provide system-generated immediate personalised nutrition reports and feedback.

### Physical activity

Physical activity (PA) will be measured using the Active Australia Survey [37]. The Active Australia Survey is used by the Australian Institute of Health and offers short and reliable questions to measure leisure time physical activity.

### Quality of life and sleep

Quality of life (QoL) will be measured using the PROMIS GLOBAL Health Scale v1.2 (13th April, 2018, Global 10), a series of 10 questions that aims to measure QoL experienced over the last 7 days [38]. Sleep will be measured using the PROMIS short form Sleep Disturbance 4a, a four-item questionnaire that scores sleep quality and compares it to a mean score of 50 [39].

### Health literacy and patient activation measures

Two health literacy tools will be used here. eHEALS is a validated measure of eHealth literacy for older adults [40]. It is an 8-item measure that questions the participants use of internet-based resources. The All Aspects of Health Literacy Scale (AAHLS) captures general health literacy [41].

The Patient Activation Measure (PAM) is a 10–13 item measure that aims to categorise participants according to their knowledge, skills and confidence in managing their own healthcare. It can be converted into a 100-point quantifiable scale that is predictive of patient engagement with their healthcare. Responses are categorised into four broad categories that range from “disengaged and overwhelmed” to “maintaining behaviours and pushing forward”. It is appropriate for use in older adults and can demonstrate how changes in category may also affect other aspects of life [42, 43].

To ensure congruency between clinicians and patients, registered GPs and APD’s will complete the Clinician Support Patient Activation Measure (CS-PAM) [44]. The CS-PAM mirrors the questions asked in PAM but is modified to be answered from the clinician perspective.

### Other demographic and medical data

Other demographic data that may impact on heart health will be collected from the participant via a survey, including social history, living arrangements, level of education, household income and the number of dependents.

At 12 months, participants will be contacted by telephone to book in for their annual heart health assessment. At this time, participants will be asked about any GP visits regarding their heart health care in the previous 12 months and any referrals to other health care professionals.

### Biological specimens

A sub-sample of consenting participants will be asked to provide additional biological samples for future genetic testing and to correlate responses to the AES-Heart. Participants are to be chosen based whether they are able to access a pathology collection and processing site that is able to process the samples in a time frame that protects the integrity of the samples and is able to freeze the samples at -80^o^C on site.

### Intervention feasibility

Semi-structured interviews will be conducted with APDs and consenting participants after the first 6-months of the intervention to test its feasibility. Interviews will be strengths-based and continue until theme saturation. Sampling for representative demographic or geographic factors, and a thematic analysis will be performed. For all groups, questions will focus on trial experience and include acceptability and appropriateness of approach for regional/rural patients, potential improvements, and opportunities for wider adoption of MNT for CVD.

### Intervention fidelity, barriers, and enablers

Audio recordings will be collected from a sub-sample of dietetic consultations throughout the intervention. These will be used to qualitatively assess APDs for intervention fidelity specifically the negotiation of participant goals, measures of success, and identification of barriers and enablers.

### Data management

REDCap will be used to collect and store research data [45, 46]. Data will be added directly by participants or by members of the management or recruiting team. Where possible, original records will be kept electronically, to allow for checks where data outliers are identified. Data is transferred securely to and from General Practices using any method approved by the ethics committee. The study Chief Investigator, Project Manager, Statisticians and Economic Analysts associated with the analysis may have access to the final dataset. The de-identified datasets used and / or analysed during the current study may be available from the corresponding author on reasonable request.

### Statistical methods

Linear mixed models will be used to analyse changes in outcomes, with a fixed effect for arm, and random effect for individual and cluster. The effect of the intervention will be based on the coefficient of the arm by time interaction term and adjusted for primary care service.

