### Study outcomes

The primary study outcome is change from baseline in total serum cholesterol, as collected and analysed by National Associate of Testing Authority accredited pathology services in the state. Data for this outcome is collected at baseline, 3-, 6- and 12-months.

Secondary outcomes for the study include change from baseline for:

i)Serum low density lipoprotein (LDL) cholesterol, collected at baseline, 3-, 6- and 12-months.ii)Serum triglycerides, collected at baseline, 3-, 6- and 12-months.iii)Systolic and diastolic blood pressure, collected at baseline and 12 months after randomisation.iv)Percentage of total energy dietary intake derived from energy-dense, nutrient-poor and nutrient-dense food groups. This is measured by food frequency questionnaire and collected at baseline, 3-, 6- and 12-months after randomisation.v)Self-reported weight. This data will be collected at baseline, 3-, 6- and 12-months.vi)Self-reported waist circumference. This data will be collected at baseline, 3-, 6- and 12 months.vii)Quality of life, assessed at baseline, 3-, 6- and 12-months.

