### Power and sample size calculation

To detect a change in total cholesterol (primary outcome) of 0.51 mmol/L (SD = 1.1) [31], with 80% power and alpha 0.05, 74 people are needed. Allowing for a 25% drop out requires 100 people per group. To account for clustering by GP practice, we assume 10 practices per arm, each contributing 10 people. The design effect, assuming an ICC of 0.05 is 1.45, meaning a final sample size of 145–150 people per arm (15 practices per arm, each contributing 10 people) for a total of 300 patients is required.

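### As worded, the primary model has no term for practice-to-practice variation in change, so the arm-by-time test would ordinarily omit the clustering that the sample size pays for; if the ICC of 0.05 applies to change, the 5% test runs at about 9% to 10%

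*Protocol article*

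**What the plan says.** The Statistical methods section of the protocol article sets out the primary analysis in two sentences. The first gives the model: "Linear mixed models will be used to analyse changes in outcomes, with a fixed effect for arm, and random effect for individual and cluster". The second gives the test: "The effect of the intervention will be based on the coefficient of the arm by time interaction term", and adds an adjustment for the primary care service. No practice-by-time random effect, practice-level slope or cluster-robust variance is named. The random effects are not expressly described as intercepts.

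Under Study outcomes, "The primary study outcome is change from baseline in total serum cholesterol", measured at baseline, 3, 6 and 12 months.

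Under Power and sample size calculation, the target is framed as a change: "To detect a change in total cholesterol (primary outcome) of 0.51 mmol/L (SD = 1.1", and "with 80% power and alpha 0.05, 74 people are needed". Then "Allowing for a 25% drop out requires 100 people per group", and for clustering by practice "The design effect, assuming an ICC of 0.05 is 1.45". The final layout is "15 practices per arm, each contributing 10 people".

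**The concern.** An arm-by-time coefficient compares follow-up with baseline within people. Anything that moves all visits of a person, or all visits of a practice, by the same amount subtracts out of it. The clustering that matters for this coefficient is therefore not that some practices have higher cholesterol than others. It is that patients of one practice may change more, or less, than patients of another. That variation needs its own term, and none is named.

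The sample size section treats the outcome as clustered by practice and enlarges the trial by 45% for it. If the analysis leaves that clustering out, the primary standard error is too small, the confidence interval too narrow, and the false-positive rate above 5%.

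**Working it through.** **1. The plan's own sample size.** Inputs from Power and sample size calculation: difference 0.51, SD 1.1, alpha 0.05 (taken as two-sided), power 80%, dropout 25%, ICC 0.05, 10 patients per practice.

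- n per arm = 2 × (1.96 + 0.8416)² × (1.1/0.51)² = 73.03, rounded up to 74. This agrees.
- Dropout: 74/0.75 = 98.7, so 99 (stated as 100).
- Design effect: 1 + (10 − 1) × 0.05 = 1.45. This agrees.
- 100 × 1.45 = 145, rounded to 15 × 10 = 150 per arm. This agrees.

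**2. What cancels.** Take the stated model with intercepts, for patient i in practice j at visit t:

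Y(ijt) = fixed effects + c(j) + b(ij) + e(ijt)

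Change from baseline is Y(ij,t) − Y(ij,0) = fixed part + e(ijt) − e(ij0). Both c(j) and b(ij) are gone. A fixed practice effect used as the adjustment goes the same way. With complete data the model's standard error for the contrast is thus that of a comparison of individual changes that ignores practice. A mixed-model fit to one simulated balanced data set confirmed this: 0.1255 from the model and 0.1255 from the practice-blind comparison. Some optimiser warnings appeared in the model-fitting run; the closed-form results below do not depend on it.

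**3. Size of the understatement.** Let ρ be the ICC of change and m the patients analysed per practice. The correct variance is the model's variance times D = 1 + (m − 1)ρ. The standard error is understated by 1 − 1/√D, and the actual error rate of a nominal 5% test is 2 × [1 − Φ(1.96/√D)].

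| ρ | m | D | SE understated by | Actual type I error |
|---|---|---|---|---|
| 0.05 | 10 | 1.45 | 17% | 10.4% |
| 0.05 | 7.5 (after 25% dropout) | 1.325 | 13% | 8.9% |
| 0.02 | 10 | 1.18 | 8% | 7.1% |
| 0.10 | 10 | 1.90 | 27% | 15.5% |

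The rows at 0.02 and 0.10 are assumed values, to show sensitivity. Simulation with 10,000 runs, 15 practices per arm, 10 patients each and ρ = 0.05 gave 10.2% with two visits and 10.5% with four. A t-test on practice mean changes in the same data gave 5.0% and 5.2%.

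**4. If 0.05 is the ICC of cholesterol level.** The ICC of change then depends on how stable the practice effect is over time (cluster autocorrelation, CAC) and how stable the patient effect is (individual autocorrelation, IAC):

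ρ(change) = 0.05(1 − CAC) / [0.05(1 − CAC) + 0.95(1 − IAC)]

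The protocol gives neither, so the values below are assumptions, with IAC from 0.5 to 0.8.

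| CAC | ρ of change | Type I error, m = 10 | Type I error, m = 7.5 |
|---|---|---|---|
| 1.0 | 0 | 5.0% | 5.0% |
| 0.9 | 0.010 to 0.026 | 6.1% to 7.7% | 5.8% to 7.0% |
| 0.8 | 0.021 to 0.050 | 7.2% to 10.4% | 6.6% to 8.9% |
| 0.5 | 0.050 to 0.116 | 10.4% to 17.1% | 8.9% to 13.9% |

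**5. If the response is a change score.** With one follow-up time and a practice intercept, clustering of change is in the model, and simulation gave about 5.8% (Wald z). But that model has no arm-by-time term. With change scores at 3, 6 and 12 months, the arm-by-time term compares one follow-up with another: the practice intercept cancels again, and the coefficient is no longer the treatment effect.

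**The case against.** The best defence is that the article does not pin down the faulty model. It speaks of a random effect, not a random intercept, so a practice slope or practice-by-time effect is not excluded. It speaks of analysing changes, which could mean change scores. The adjustment for primary care service might be meant as cluster adjustment of the treatment effect itself. An analysis plan that is not shown may spell out the structure, and degrees-of-freedom methods usually belong there.

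Part of this stands. The wording does not prove that intercepts alone will be fitted, and a reader should not infer that the trial's analysis certainly ignores clustering. But the article does more than leave detail open: it names the random effects and it names the coefficient to be tested. Read in the ordinary way, the two do not fit together, and an analysis plan that carried out those sentences as written would inherit the fault. The change-score reading does not repair this (step 5 of the working), and adjustment through a practice main effect cancels like the intercept.

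A second objection is that the documents do not say whether 0.05 is the ICC of change or of level. This also stands, and it makes any single error rate conditional. It does not remove the problem: on the level reading the test is correct only if practice effects do not vary over time at all.

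**Conclusion.** The point holds in conditional form. As worded, the primary analysis contains no term for between-practice variation in change, while the sample size is inflated by 1.45 for clustering by practice. Given random intercepts only and an ICC of 0.05 for change, the standard error is 13% to 17% too small. The nominal 5% test then runs at 8.9% (7.5 completers per practice) to 10.4% (10 per practice), and a nominal 95% interval covers about 91% to 90%.

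A reader might infer that the test simply runs at 10%, double its nominal rate. The documents do not support that as a flat statement. It needs intercepts only, the ICC applying to change, and no loss of patients from the practices, whereas the protocol itself plans for 25% dropout. If 0.05 is the ICC of level, the rate starts at 5% and depends on an autocorrelation that the protocol does not give. Applying the ICC to change is nevertheless the reading closest to the sample size section, which frames its target as a change in cholesterol.

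**What to change.** In Statistical methods, add a random practice-by-time effect to the practice and participant effects. If time is modelled as linear, a practice-level random slope does the same job; a practice-level analysis of change is an equivalent alternative. Base the test and interval on small-sample degrees of freedom tied to the number of practices, for example by Kenward-Roger or Satterthwaite: with 30 practices in two arms, about 30 − 2 = 28. State also whether the ICC of 0.05 refers to change or to level.

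This is a short change of text. The interval becomes wider than under intercepts only, by a factor of about √1.325 = 1.15 to √1.45 = 1.20 at the planned ICC, before the small effect of the degrees of freedom. The design already allows for this. After 25% dropout there are 150 × 0.75 = 112.5 patients per arm, worth 112.5/1.45 = 77.6 independent patients even at the full design effect, against the 74 required. If practices hardly differ in change, the added term costs little.

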#### Health professionals delivering the intervention

The MNT intervention will be delivered by APDs. Dietitians wishing to practice privately in Australia must hold APD status with Dietitians Australia [35], thus an APD qualification requirement ensures the study is consistent with the current healthcare setting standards. APDs employed in the study must have completed continuing professional development modules that cover telehealth practice, and CVD nutrition. They must also work in a rural area classified as MM 3–6 or be able to demonstrate they have provided continuity of care to a rural community within the previous five years. Employed APDs will also have the capacity to provide continuous care over the course of the participant’s five scheduled consultations. Participants will have the same APD throughout their five consultations, unless a change is requested by the participant, in order to assist in building rapport with participants and ensure that advice pertinent to the participants’ situation is provided.

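### The stated mixed model has no term for clustering by dietitian in the intervention arm; if outcomes correlate within dietitian and dietitians serve several practices, the standard error would be understated

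*Protocol article*

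**What the plan says.** Under Statistical methods, the article specifies linear mixed models "with a fixed effect for arm, and random effect for individual and cluster". The treatment effect is the arm-by-time coefficient, adjusted for primary care service. Practices are the unit of randomisation (Methods; Randomisation), so the cluster is the practice, and the adjustment is also at practice level.

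The Power and sample size calculation section takes the same view of clustering: "To account for clustering by GP practice, we assume 10 practices per arm, each contributing 10 people". No other source of clustering is allowed for.

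The Intervention group section gives APD consultations to the intervention arm only. The section on the health professionals delivering the intervention adds: "Participants will have the same APD throughout their five consultations", unless the participant asks for a change. That section speaks of APDs in the plural. It gives no number, no caseload and no rule for allotting them to practices.

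**The concern.** People treated by the same dietitian may have more similar outcomes than people treated by different dietitians, because goals are negotiated and advice is tailored by that dietitian. The article itself plans to assess APDs from recorded consultations for fidelity in goal negotiation, so it treats delivery as something that can vary. Such correlation could arise only in the intervention arm.

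A practice random effect picks it up fully only when practice and APD coincide. Consultations are by video call or telephone, and an APD need not work in the participant's town, so one APD could plausibly serve several practices. The practice effect would then absorb the APD variance partly (if whole practices share an APD) or hardly at all (if APDs are crossed with practices).

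At stake is the confidence interval for the primary outcome. An error from this source runs one way, towards too narrow an interval, in a trial meant to inform policy on wider provision of telehealth nutrition therapy.

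**Working it through.** **The plan's own figure.** Inputs from the Power and sample size calculation section: difference 0.51 mmol/L, SD 1.1, 80% power, alpha 0.05 (taken as two-sided), 25% dropout, practice ICC 0.05, 10 people per practice.

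- Per arm: 2 × (1.1/0.51)² × (1.960 + 0.842)² = 73.03, rounded up to 74. This matches "with 80% power and alpha 0.05, 74 people are needed", read as per arm.
- Dropout: 74/0.75 = 98.7, so 99; the article states 100.
- Design effect: 1 + (10 − 1) × 0.05 = 1.45, matching "The design effect, assuming an ICC of 0.05 is 1.45". Then 100 × 1.45 = 145, rounded to 15 × 10 = 150 per arm.

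The stated sample size reproduces. The point is not an arithmetic error.

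**What an APD effect would add.** Assumptions not in the article: K = 3, 5 or 8 APDs with equal caseloads, crossed with practices; APD ICC (ρ) of 0 to 0.05; one follow-up time.

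- Completers per arm: 15 practices × 7.5 = 112.5.
- Design effect among completers: 1 + (7.5 − 1) × 0.05 = 1.325.
- Variance of the difference that the practice-only model recognises, in SD² units: 2 × 1.325/112.5 = 0.0236. The standard error is 1.1 × √0.0236 = 0.169 mmol/L.
- Omitted variance, intervention arm only: ρ/K.
- Factor by which the standard error is understated: √(1 + (ρ/K)/0.0236).
- Type I error: two-sided t tail on 28 df (30 practices − 2) beyond 2.048 divided by that factor.

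Example, K = 3 and ρ = 0.05: ρ/K = 0.0167; √(1 + 0.0167/0.0236) = 1.31; type I error 12.8%.

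| APDs | ρ = 0 | ρ = 0.01 | ρ = 0.02 | ρ = 0.05 |
|---|---|---|---|---|
| 3 | 1.00 (5%) | 1.07 (6.5%) | 1.13 (8.1%) | 1.31 (12.8%) |
| 5 | 1.00 (5%) | 1.04 (5.9%) | 1.08 (6.9%) | 1.19 (9.7%) |
| 8 | 1.00 (5%) | 1.03 (5.6%) | 1.05 (6.2%) | 1.12 (7.9%) |

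Each cell gives the factor, with type I error in brackets.

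**Check by simulation.** 20,000 trials per setting, 15 practices per arm, 8 completers each, t-test on practice means. Type I error at ρ = 0.01, 0.02 and 0.05:

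- 3 APDs crossed with practices: 6.9%, 8.5%, 13.4%. Assigned by whole practice: 6.3%, 7.6%, 11.5%.
- 5 APDs crossed: 5.9%, 7.0%, 10.0%. By whole practice: 5.9%, 6.4%, 8.1%.
- A separate APD for each of 15 practices: 5.4%, 5.0%, 4.9%.
- ρ = 0, any setting: 4.8% to 5.2%.

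**The case against.** **The two conditions are not documented.** Understatement needs an APD ICC above zero and APDs shared across practices, and the article states neither. It also limits variation between APDs: a common qualification, required training modules, set session timing and topics, system-generated reports as the starting point, and a fidelity assessment. This stands. It does not make the ICC zero, but no section supports 0.05 in particular, and at 0.01 with 5 to 8 APDs the factor is only 1.03 to 1.04.

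**The null behind the type I error is unusual.** If the intervention changes nobody's cholesterol, APDs cannot differ in their effect. The inflation concerns a zero average effect with some APDs lowering and others raising cholesterol. At ρ = 0.05 the SD between APDs would be √0.05 × 1.1 = 0.25 mmol/L, which is large beside a target of 0.51. This is a good reason to read the upper end with caution. It does not remove the point, because the interval would be too narrow whatever the average effect.

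**The calculation is not the planned estimator.** It uses one time point, whereas the plan uses an arm-by-time coefficient from repeated measures. This stands, so the factors are approximate. A reader might infer that even one APD per practice would leave the model wrong, since an APD acts on change after baseline and a practice random intercept alone would not capture that. The article does not say whether the practice effect is an intercept only, so this is not claimed.

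**A condensed article may leave provider effects to a fuller plan.** It may. But the random effects are listed explicitly, and the list as written can be judged.

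**Conclusion.** The omission is real: the listed random effects cover individual and practice, while the intervention arm has a further level that the control arm lacks. The consequence is conditional. If outcomes correlate within APD and an APD serves several practices, the standard error of the arm-by-time effect would be understated and the type I error would exceed 5%. Under the assumptions shown, the range runs from no effect to a factor of about 1.3 and a type I error of about 13%.

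A reader might go further and conclude that the standard error is too small, that the interval will be too narrow, or that only a few APDs are employed. The article supports none of these, because the number of APDs, their allotment and the APD ICC are all unstated. Nor does the point show the sample size to be miscalculated on its stated assumptions. This is a worthwhile, inexpensive improvement to the analysis plan, held with medium confidence.

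**What to change.** - Record the APD for each intervention participant, and state how many APDs are employed and how they are allotted to practices.
- Prespecify, before outcome data are seen, a partially nested version of the mixed model: an APD random effect in the intervention arm only (APD variance zero in control), with small-sample degrees of freedom.
- Settle its role in advance by the number of APDs. If there are enough to estimate the variance, make it the primary model. If not, keep the practice-only model as primary, run the APD model as a prespecified sensitivity analysis, report the APD ICC, and limit the conclusion to the APDs employed. That limit matters because the possible error is largest when APDs are few, which is also when the variance is hardest to estimate.

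The cost is a sentence or two in the analysis section and one variable per intervention participant. The article does not say whether that variable is already held. The interval may be somewhat wider, and the APD variance will be imprecise if APDs are few. Neither the sample size nor the delivery of the intervention needs to change.

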## Methods

The current study is a parallel group 12-month cluster randomised controlled trial (RCT) that compares provision of two levels of dietary advice within a rural primary care setting. Primary care practices are randomised such that patients in the first group will receive usual care as provided by their General Practitioner (GP), with the addition of a dietary assessment via a food frequency questionnaire (FFQ) which includes an individualised automated feedback report on usual eating patterns. The second group will also receive individualised feedback from the FFQ, and an additional five telehealth MNT consultations over a six-month period with an APD.

The aim of this trial will be to reduce serum lipids associated with CVD health. The secondary aim will be to reduce modifiable risk factors related to CVD health, such as blood pressure, anthropometry and improve dietary patterns based on the proportion of total energy contributed by foods from food groups that are energy-dense, nutrient-poor and also those that are nutrient-dense.

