### Randomisation

General Practices recruited to the project will be stratified to ensure samples are representative.

i)Practices will firstly be stratified by MM categories 3–5.ii)Practices will also be stratified by practice size according to the following criteria: (1) small practice (1–5 GPs in the practice at the time of registration) and (2) medium to large practice (more than 5 GPs working in the practice at the time of registration).

A randomisation procedure for the practices was developed by a statistician external to the project, with practices being assigned to either the intervention or control arm. The randomisation module was uploaded into the research REDCap database, by an external REDCap administrator, so that all researchers are blinded until randomisation takes place. Practices and participating GPs will be unaware of the allocation of their group until at least one GP from the practice has registered. Other GPs from the same practice may register with the study after the allocation is known, for example when a new registrar joins the practice.

Recruitment of practices will continue until the target number of participants is met, or no further practices are available to be approached.

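### The stated model omits both randomisation strata, and its only named adjustment is undefined and seems to repeat the practice random effect

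*Protocol article*

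**What the plan says.** All of this is in the protocol article.

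- **Unit of randomisation (Methods, opening paragraph).** "Primary care practices are randomised such that patients in the first group will receive usual care". The practice is therefore the cluster.
- **Strata (Randomisation).** "Practices will firstly be stratified by MM categories 3–5", and "Practices will also be stratified by practice size according to the following criteria": one to five GPs, or more than five. This gives 3 × 2 = 6 cells.
- **Model (Statistical methods).** A linear mixed model "with a fixed effect for arm, and random effect for individual and cluster". The intervention effect is the coefficient of the arm-by-time "interaction term and adjusted for primary care service".

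MM category and practice size do not appear under Statistical methods. The term for the adjustment variable is not defined anywhere in the article.

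**The concern.** Factors that constrain the allocation normally belong in the analysis. Stratifying removes between-stratum differences from the true sampling variation of the treatment contrast. If the model omits the strata, those differences stay in the error term, so the standard error is larger than the design warrants.

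Here the article does name an adjustment, but it appears to be the randomised unit rather than the factors used to stratify it. There are two readings:

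- It restates the random cluster effect. The phrase is then redundant, and the model has no adjustment for the strata.
- It is a further fixed effect for practice. It then duplicates the random term and conflicts with the fixed arm effect named in the sentence before it, because every practice lies wholly in one arm.

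At stake are some precision in the primary comparison and a model statement that two analysts could implement differently.

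**Working it through.** **1. The plan's own figures.** Power and sample size calculation gives a difference of 0.51 mmol/L, SD 1.1, 80% power, alpha 0.05, 25% dropout, ICC 0.05 and 10 people per practice.

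- n per arm = 2 × (1.96 + 0.842)² × 1.1² / 0.51² = 73.03, rounded up to 74 (two-sided). Stated: 74.
- 74 / 0.75 = 98.7, so 99. Stated: 100.
- Design effect = 1 + (10 − 1) × 0.05 = 1.45. Stated: 1.45.
- 100 × 1.45 = 145. Stated: 145–150 per arm, with 15 practices of 10 in each.

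The sample size reproduces and is not in question.

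**2. Practice as a fixed effect.** Rank of the fixed-effects design matrix for 30 practices × 10 people × 4 visits:

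| Terms | Columns | Rank |
|---|---|---|
| practice + time | 33 | 33 |
| + arm | 34 | 33 |
| + arm × time | 37 | 36 |
| practice + six stratum cells (no time) | 35 | 30 |

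Adding arm does not raise the rank, so the arm main effect is fully aliased with practice, as are stratum main effects. The three arm-by-time terms each add one to the rank, so the planned effect remains estimable.

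**3. Leaving out the strata.** The simulation took practice mean changes for 30 practices in six strata (sizes 6, 4, 6, 4, 6, 4), allocated 1:1 within each, with 10 × 0.75 = 7.5 completers per practice. SD 1.1 and ICC 0.05 were applied to change. The share of between-practice variance due to strata is an assumption; the documents give no figure. The adjusted analysis fits all six cells.

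| Share | Type I, without | Type I, with | Power, without | Power, with |
|---|---|---|---|---|
| 0% | 0.051 | 0.051 | 0.829 | 0.823 |
| 25% | 0.044 | 0.050 | 0.842 | 0.849 |
| 50% | 0.036 | 0.050 | 0.847 | 0.873 |
| 100% | 0.027 | 0.051 | 0.872 | 0.930 |

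The power differences are −0.7, 0.7, 2.6 and 5.9 points. The last row is the extreme case, in which the strata explain all variation between practices.

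**4. Hand check of the 50% row.** Between-practice variance = 0.05 × 1.21 = 0.0605. Within-practice variance of a mean = 0.95 × 1.21 / 7.5 = 0.1533. Half of 0.0605 (0.0303) belongs to the strata, so the variance left is 0.0303 + 0.1533 = 0.1835. An analysis without strata uses about 0.0605 + 0.1533 = 0.2138. The test statistic shrinks by √(0.1835 / 0.2138) = 0.926. The critical value 2.048 (28 df) acts like 2.048 / 0.926 = 2.21, a two-sided type I error of about 0.035. The simulation gave 0.036.

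**The case against.** The case against has four parts.

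- **The article never calls practice a fixed effect.** The ordinary reading is that the phrase restates the random cluster term. This stands: aliasing is conditional on a reading that the text permits but does not state.
- **A reader might infer that the primary analysis cannot be estimated.** The documents do not support that. The effect is the arm-by-time coefficient, which stays estimable even with practice fixed (step 2). A model of follow-up values alone would fail, but none is proposed.
- **A reader might infer a sizeable variance gain from a lower ICC.** If strata explained 20–40% of between-practice variance, the ICC would fall to 0.04–0.03 and the design effect to 1 + 9 × 0.04 = 1.36 or 1 + 9 × 0.03 = 1.27. The ratios to 1.45 are 0.938 and 0.876, seemingly 6–12% less variance. That does not carry over. A lower ICC for cholesterol level says nothing direct about an arm-by-time contrast, from which stable practice differences cancel. A gain needs strata that predict change, and nothing in the documents shows that they do.
- **A short article may leave the covariate list to the SAP.** This is partly right, since the text does not exclude the strata. But the article does commit to an adjustment, and what it commits to is unclear and appears to sit at the wrong level. That can be judged as it stands.

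Stratified allocation also limits imbalance on these two factors by design, so uncorrected imbalance is not a strong argument here.

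**Conclusion.** The point holds, at modest size. The model as stated omits both randomisation strata, and its one named adjustment is undefined and probably redundant.

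The consequence is a somewhat conservative test and a small loss of precision, and only if MM category or practice size predicts change in cholesterol. With an assumed share of 25–50% at ICC 0.05, type I error is about 0.044–0.036 and the power loss 0.7–2.6 points. If the strata predict nothing, adjustment gains nothing and costs about 0.7 points in this simulation.

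Bias or an inflated type I error might be inferred, but neither follows: every type I figure without the strata is at or below the nominal level, within simulation error.

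The figures are illustrative. They rest on the assumed share, on ICC and SD applied to change, and on an analysis of practice mean changes standing in for the mixed model.

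**What to change.** In Statistical methods:

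1. State that practice enters as a random effect only. Delete the adjustment for primary care service, or define it if something other than the practice is meant.
2. Add fixed effects for MM category and practice size. If baseline stays in the outcome vector, include their interactions with time, because stratum main effects alone would do little for the arm-by-time contrast. In a change-score or baseline-adjusted model, main effects are enough.
3. Reconcile the MM range. Study participants and eligibility admits practices in MM 3–6, whereas Randomisation stratifies MM 3–5. An MM 6 practice has no stated stratum, so its covariate value is undefined until the two agree.

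Cost: a sentence or two. Both variables are needed for the stratified allocation, so no new data are required. The main effects use 2 + 1 = 3 of the 30 − 2 = 28 between-practice degrees of freedom; the simulation, which fitted six cells, spent 5. The downside is a slight loss of power if the strata are not prognostic. The planned sample size does not change.
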